### Study Interventions and Anesthesia

The schedule of enrollment, interventions, and assessments in accordance with the SPIRIT 2013 statement is shown in Table 1. The baseline blood pressure is obtained by independent nursing personnel when patients are comfortably seated in surgical wards before the day of surgery. According to the web-based centralized randomization list, patients will take the study medications (either the ACEIs/ARBs or placebo pills) orally on the morning of surgery. The time of study medication will be documented.

**Table 1 T1:** Schedule of enrollment, interventions, and assessments.

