### Outcome Measures

The primary outcome measure of this trial is the incidence of perioperative hypotensive events, defined as MBP <65 mmHg or ≥30% reduction in MBP from baseline for which an intervention is needed (including intravenous fluids infusion and/or use of vasopressors), which occur during surgery and in the PACU.

The secondary outcome measures are: (1) duration of perioperative hypotension, (2) intraoperative use of fluids and vasopressors, (3) postoperative hypotensive events in the surgical wards within 3 days after surgery, and (4) perioperative neurocognitive disorders (PND), major adverse cardiocerebral events (MACEs, a composite outcome of permanent or transient stroke, coma, myocardial infarction, heart block, and cardiac arrest), and mortality within 30 days after surgery. MACE will be assessed as a composite outcome, and each complication will also be assessed individually, according to the definitions in Table 2.

**Table 2 T2:** Definitions of postoperative complications.

**Event**	**Definition**
PND	Indicates perioperative neurocognitive disorders assessed using the CAM-ICU until ICU discharge or using the CAM in the surgical wards and at 30 days after surgery.
MACEs	Indicates a composite outcome of permanent or transient stroke, coma, myocardial infarction, heart block, and cardiac arrest.
Stroke	Indicates a postoperative stroke (i.e., any confirmed neurological deficit of abrupt onset caused by a disturbance in blood supply to the brain).
Coma	Indicates a new postoperative coma that persists for at least 24 h secondary to anoxic/ischemic and/or metabolic encephalopathy, thromboembolic event or cerebral bleed.
Myocardial infarction	Indicates a myocardial infarction event documented by at least one of the following criteria: 1. evolutionary ST-segment elevations; 2. development of new Q-waves in two or more contiguous ECG leads; 3. new or presumably new left bundle branch block pattern on the ECG; 4. cardiac Troponin I > 0.05 ng/ml.
Heart block	Indicates a new heart block requiring the implantation of a permanent pacemaker of any type prior to discharge.
Cardiac arrest	Indicates an acute cardiac arrest documented by one of the following: 1. ventricular fibrillation; 2. rapid ventricular tachycardia with hemodynamic instability; 3. asystole.

*PND, perioperative neurocognitive disorders; MACEs, major adverse cardiocerebral events; CAM, confusion assessment method; ICU, intensive care unit; ECG, electrocardiogram*.

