### Sample Size Estimation

The sample size calculation was performed using the PASS software (version 11.0.7, NCSS, LCC, Kaysville, UT, USA). Based on an international prospective cohort study of 4802 patients undergoing non-cardiac surgery, the incidence of intraoperative hypotensive events was 28.6% in the ACEIs/ARBs continued group (15). We hypothesize that the suspension of ACEIs/ARBs before surgery would reduce the incidence of hypotension by 20%, that is, to a hypotension rate of 22.88%. To detect such a difference with α = 0.05 and power = 80%, 916 patients per group are needed. We estimate a drop-out rate of 10%, and thus 1,018 patients will be enrolled in each group.

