### Statistical Analysis

Data distribution and normality will be assessed with Shapiro-Wilk test. Continuous variables will be presented as mean ± standard deviation or median (interquartile ranges), depending on their distribution. Categorical variables will be presented as number (percentages). All analyses will follow the intention-to-treat principle, which includes all participants after randomization and excludes the patients who drop out of the study due to withdrawal of informed consent or cancellation of surgery. The per-protocol analysis will be carried out as a sensitivity analysis, which includes all participants with planned interventions and minimal protocol violation. As we expect that the missing data will be uncommon in our dataset, there will be no plan for imputation of missing data.

The primary outcome of perioperative hypotension occurrence will be assessed using multivariate logistic regression adjusting for the following baseline covariates: age, body mass index, ASA status, hypertension grade, previous myocardial infarction, atrial fibrillation, diabetes mellitus, hemoglobin value, use of diuretics, and trial site. The odds ratio with 95% confidence intervals will be reported.

In addition, subgroup analyses for the primary outcome will be conducted to explore whether the effects of study interventions will vary, according to six variables: age, hypertension grade, diabetes mellitus, type of surgery, duration of surgery, and trial site. The interaction analysis of effects across the subgroups will be performed using a test of treatment-by-covariate interaction on a logistic regression model.

For the secondary outcomes, analysis will be conducted using generalized linear model for continuous variables or using multivariate logistic regression for binary variables, adjusting for the above-mentioned baseline covariates. The Benjamini-Hochberg procedure will be used to control the false-discovery rate for multiple comparisons. The *P*-values before and after correction will be presented. For the exploratory outcomes, only descriptive statistics will be applied, without multiple testing or statistical inference.

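### One exploratory subgroup is defined by duration of surgery, which is observed after treatment; a false interaction would need the delay per episode to differ by arm, so the point is minor

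*Protocol article*

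**What the plan says.** All references are to the protocol article.

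- **Statistical Analysis** states that "subgroup analyses for the primary outcome will be conducted to explore whether the effects of study interventions will vary". The factors that define these subgroups are then listed: the analysis proceeds "according to six variables: age, hypertension grade, diabetes mellitus, type of surgery, duration of surgery, and trial site". The method is "a test of treatment-by-covariate interaction on a logistic regression model". The text does not say whether duration is scheduled or actual, gives no cut, and attaches no caution to this variable.
- **Study Interventions and Anesthesia** fixes the time of treatment: "patients will take the study medications (either the ACEIs/ARBs or placebo pills) orally on the morning of surgery".
- **Outcome Measures** counts a low pressure as a primary event when it is one "for which an intervention is needed (including intravenous fluids infusion and/or use of vasopressors), which occur during surgery and in the PACU".
- **Statistical Analysis** lists the covariates of the primary model as "age, body mass index, ASA status, hypertension grade, previous myocardial infarction, atrial fibrillation, diabetes mellitus, hemoglobin value, use of diuretics, and trial site". All are baseline variables, and duration of surgery is not among them.

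**The concern.** A subgroup comparison keeps the protection of randomisation when the subgroup is fixed before treatment. Age, hypertension grade, diabetes and trial site clearly are, and type of surgery is on its natural reading. Actual duration of surgery is not. It becomes known only after the capsule has been taken, and it accrues over much of the window in which the primary outcome is counted. An event must need fluids and/or vasopressors, so managing it could take operating time. Treatment could also affect duration by some other route.

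If so, the patients in the short or the long stratum may differ between arms in ways that randomisation did not balance. At stake is the reading of one interaction test: a report that withholding helps mainly in long operations, when the true effect is the same in all patients.

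**Working it through.** **1. Inputs from the article.** Sample Size Estimation gives event rates of 28.6% (continued) and 22.88% (withheld), 916 patients per group, and 1,018 after 10% drop-out. Statistical Analysis uses a two-sided 0.05 threshold.

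**2. The plan's own figure.** Pooled-variance formula, with mean rate 0.2574 and difference 0.0572:

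n = [1.960 × √(2 × 0.2574 × 0.7426) + 0.8416 × √(0.286 × 0.714 + 0.2288 × 0.7712)]² / 0.0572² = (1.2118 + 0.5193)² / 0.003272 ≈ 916.

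Then 916 / 0.9 = 1,017.8, so 1,018. The sample size reproduces, and this point does not affect it. The implied odds ratio is (0.2288/0.7712) / (0.286/0.714) = 0.741.

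**3. What conditioning on duration does to an odds ratio.** Let T = 1 for withheld, Y = 1 for a hypotensive event, and L = long surgery. By Bayes' rule, the odds ratio in the long stratum is

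OR(L) = OR × [P(L | Y=1, T=1) × P(L | Y=0, T=0)] / [P(L | Y=1, T=0) × P(L | Y=0, T=1)].

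- If an event lengthens surgery equally in both arms, and risk does not depend on underlying duration, P(L | Y, T) depends on Y alone. The multiplier is then 1, and likewise in the short stratum: no distortion.
- If the delay differs by arm, the multiplier is not 1. Worked case (assumed: duration normal, mean 150 min, SD 60, cut 180, an event adds 15 min in the continued arm only): P(L) = P(Z > 0.5) = 0.309 in three cells and P(Z > 0.25) = 0.401 for continued patients with an event. Long: 0.741 × 0.309/0.401 = 0.57. Short: 0.741 × 0.691/0.599 = 0.86. A uniform effect appears as two different effects.
- If treatment alone shifts duration, the multiplier is again 1, unless underlying duration also predicts the event. The next step allows for that.

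**4. Simulation of the test.** 916 per arm, 4,000 trials per scenario, constant conditional odds ratio 0.741, so no true effect modification. Test statistic: (log OR long − log OR short) / √(sum of 1/count over the eight cells), rejecting beyond 1.96. Everything about duration is assumed:

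- Set A: underlying duration lognormal, median 120 min, log-SD 0.5, cut 120, log odds rising 0.8 per unit of log duration.
- Set B: normal, mean 150 min, SD 60, cut 180, log odds rising 0.5 per SD.

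| Scenario | Set A: rejection; OR long / short | Set B: rejection; OR long / short |
|---|---|---|
| Duration unaffected by treatment or event | 5%; 0.74 / 0.75 | 5%; 0.74 / 0.75 |
| Event adds 30 min in both arms | 5%; 0.74 / 0.74 | 5%; 0.74 / 0.74 |
| Event adds 2 min, continued only | 5%; 0.73 / 0.77 | not run |
| Event adds 5 min, continued only | 10%; 0.71 / 0.81 | not run |
| Event adds 15 min, continued only | 52%; 0.64 / 0.99 | 46%; 0.60 / 0.91 |
| Event adds 30 min, continued only | 99%; 0.56 / 1.49 | 95%; 0.51 / 1.16 |
| Withholding itself shortens surgery by 15 min | 5%; 0.79 / 0.79 | 5%; 0.82 / 0.79 |

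The bias toward 1 in the last row follows from the assumed direction. If withholding lengthened surgery by 15 min, Set A gives 0.70 / 0.69, again with 5% rejection.

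**The case against.** A reader might infer that any dependence of duration on hypotension makes this test misleading, or that patients within the strata are certainly no longer comparable. Neither holds. With an equal delay in both arms, the test keeps its size and both subgroup odds ratios stay near 0.74. The large rejection rates need an arm-specific delay, and nothing in the article gives any delay, let alone a difference between arms. Randomization and Blinding masks anesthesiologists and surgeons, so a difference cannot come from knowing the allocation. Outcome Measures names fluids and/or vasopressors as the response and does not say that surgery is paused. All of this stands.

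It does not clear the variable. Masking does not remove a drug-related difference in how quickly an episode is corrected. The plan itself compares duration of hypotension and use of fluids and vasopressors between arms as secondary outcomes, so it treats such a difference as possible.

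Two further objections carry some weight:

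- The analysis is exploratory. This limits the severity, although a formal test is named and the Discussion mentions the subgroup analyses alongside the trial's strengths.
- A separate analysis plan may define duration as scheduled. If it does, the point is closed. The article's wording more naturally means actual duration.

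**Conclusion.** The point holds in a limited form and is minor. The article names, for a formal interaction test, a variable that on its natural reading is observed after treatment, so the comparison within its strata is not protected by randomisation.

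The size is unknown. Under the assumed duration models, false rejection runs from about 5% when the delay per episode differs by 0 to 2 minutes between arms, to about 10% at 5 minutes, about half at 15 and nearly always at 30. A direct 15-minute shortening by withholding would leave the test at 5% but pull both odds ratios to about 0.79. These figures show what could happen; the documents do not support presenting the upper end as expected. They also rest on an unadjusted two-stratum test with an assumed cut.

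One of six exploratory subgroups is affected. The primary estimate, alpha and sample size are not.

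**What to change.** If scheduled duration was recorded before randomisation for all patients, define the subgroup by it and fix the cut in the analysis plan before unblinding. In the simulations, a duration unaffected by treatment or event keeps the test at about 5% and both odds ratios near 0.74.

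The article does not show that scheduled duration is available. Neither the schedule of assessments (Table 1) nor Data Collection lists it, and recruitment began in November 2020. If it is not available for everyone, remove duration from the interaction tests and rely on type of surgery, which is already listed, taken as the planned procedure. Report actual duration by arm descriptively, label it as post-randomisation, and draw no conclusion about effect modification from it.

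The cost is a line or two in the analysis plan and the loss of one exploratory subgroup by actual duration.

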## Discussion

In this multicenter, randomized, double-blind, placebo-controlled trial of older hypertensive adults undergoing noncardiac surgery, the primary objective is to evaluate the effects of withholding vs. continuing ACEIs/ARBs before surgery on the incidence of perioperative hypotensive events which occur during surgery and in the PACU. In addition, we will analyze the duration of perioperative hypotension, intraoperative use of fluids and vasopressors, hypotensive events within postoperative 3 days, and the rates of PND, MACEs, and mortality within 30 days after surgery. This trial will follow the Consolidated Standards of Reporting Trials (CONSORT) guideline (21).

Hypotension is significantly associated with postoperative myocardial infarction, acute kidney injury, and death (22–25). In addition, the duration of hypotension was significantly associated with postoperative stroke for patients undergoing non-cardiac and non-neurosurgical procedures (26). Randomized studies also confirmed that interventions targeting an optimal blood pressure reduced the risk of organ dysfunction after major non-cardiac surgery (27, 28). In a recent study of 955 patients with coronary artery disease and mean age of 69.7 years undergoing major non-cardiac surgery, perioperative hypotension independently predicts cardiovascular events (myocardial infarction or cardiovascular death) within 30 days after surgery (29). Older hypertensive patients have impaired autoregulation of blood flow in the vital organs (such as heart, brain, and kidneys) and are at increased postoperative risk, so perioperative blood pressure management is extremely important. Strategies that limit perioperative hypotension contribute to the improvement of postoperative outcomes.

There are no firm recommendations on the use of ACEIs/ARBs in the perioperative period, because high level of evidence such as a randomized controlled trial with a large sample size is lacking. Previous observational studies suggested that withholding ACEIs/ARBs was associated with a lower incidence of intraoperative hypotension and a reduced risk of 30-day vascular events and all-cause mortality (14, 15). However, a recent cohort study did not show an association between ACEIs/ARBs use and hypotension after general anesthesia induction in non-cardiac surgery (18). In addition, an open-label randomized trial suggested that preoperative ACEIs/ARBs management strategies did not affect vasoactive agent use or postoperative outcomes for cardiac surgical patients (19). In a recent meta-analysis of 5 randomized controlled trials and 4 cohort studies in non-cardiac surgery, continuing ACEIs/ARBs was associated with an increased incidence of intraoperative hypotensive events, but an association between ACEIs/ARBs use and major cardiac events or mortality was not found (30). Of note, the associated increase in hypotensive events in the ACEIs/ARBs continued group was mainly based on observational studies. In fact, only 3 randomized trials with a total of 75 patients reported intraoperative hypotension in this meta-analysis (11, 13, 31). A significant limitation of observational data is that the apparent associations are often confounded by multiple factors that can be related to both exposures and outcomes, making it hard to interpret the data and offering a relatively low level of evidence for clinical practice.

To our knowledge, this is the first multicenter, randomized, double-blind, placebo-controlled trial with an adequate power to assess the impact of ACEIs/ARBs management strategies on the occurrence of perioperative hypotension and major complications in older patients undergoing non-cardiac surgery. The second strength of the present trial is that, to increase the precision of statistical estimates, the primary analysis of perioperative hypotension will be adjusted using a multivariate logistic regression model for a number of baseline covariates, based on the knowledge of the association between each variable and patient outcome. Next, to explore whether the effects of study interventions will vary for several variables, subgroup analyses for the primary outcome will be performed using a logistic regression model.

There are also some limitations. First, the primary outcome of this trial is the incidence of perioperative hypotensive events, and we designate postoperative cardiovascular and cognitive complications and mortality within 30 days after surgery as the secondary outcomes. This study would be even more impactful if a composite of cerebral and cardiovascular complications is designated as the primary outcome. However, that would increase the sample size to more than 5,400 patients in order to detect a 20% decrease in the incidence of a composite of stroke, myocardial injury, or death (α = 0.05, power = 80%), based on the previous study (15). Next, we include older adults with ASA physical status II and III, and thus the effects of withholding or continuing ACEIs/ARBs strategies on patients who are sicker (i.e., ASA status IV) need to be assessed in future studies. Last, we exclude very elderly patients who are > 80 years old in this study, because we believe that further investigations on this extremely vulnerable patient population should be carried out carefully, on the basis of the results of our present study.

In conclusion, this trial is designed to determine the effects of the ACEIs/ARBs withheld strategy, as compared to the ACEIs/ARBs continued approach, on perioperative hypotension and postoperative outcomes in older patients who undergo non-cardiac surgical procedures. The implementation and reporting of this trial will be in accordance with the CONSORT guideline (21). We expect that our results will offer an evidence-based perioperative ACEIs/ARBs therapy for older hypertensive adults undergoing non-cardiac surgery.

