### Participants

At each study center, an independent preoperative investigator who is not involved in patient care or data management will screen patients' admission records to identify potentially qualified participants. Patients who meet the eligibility criteria and provide their written informed consent will be included in this study. According to the sample size estimation, a total of 2,036 eligible patients who plan to undergo non-cardiac surgical procedures will be randomly assigned, in a 1:1 ratio, to an ACEIs/ARBs continued group or an ACEIs/ARBs withheld group. Patients can withdraw their consent at any time during this study. The patient recruitment started on November 1, 2020. The expected date for completion of recruitment is December 2023. The flow chart of participants is shown in Figure 1.

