It is expected that the risk of the study interventions will not be significantly higher compared to the standard medical practice, and there is no ethically risk associated with the primary outcome assessment. Hence, interim analysis will not be performed. All analyses will be done using the SAS software (version 9.4, SAS Institute Inc., Cary, NC, USA) and R statistical software (version 3.6.0, R Foundation for Statistical Computing, Vienna, Austria), with a two-sided *P*-value < 0.05 indicating a statistically significant difference.

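### The Discussion claims adequate power for major complications, but the trial is sized for hypotension only, and its own 5,400-patient figure implies about 37–40% power for the complications composite it cites

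*Protocol article*

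**What the plan says.** - **Discussion, strengths paragraph:** the trial is presented as the first of its kind "with an adequate power to assess the impact of ACEIs/ARBs management strategies on the occurrence of perioperative hypotension and major complications".
- **Sample Size Estimation:** the only calculation is for hypotension. It starts from a cohort in which "the incidence of intraoperative hypotensive events was 28.6% in the ACEIs/ARBs continued group" and assumes a 20% relative reduction, to 22.88%. The result is: "To detect such a difference with α = 0.05 and power = 80%, 916 patients per group are needed". Then: "We estimate a drop-out rate of 10%, and thus 1,018 patients will be enrolled in each group".
- **Discussion, limitations paragraph:** complications and 30-day mortality are secondary outcomes. Of making a cerebral and cardiovascular composite primary, the article says "that would increase the sample size to more than 5,400 patients in order to detect a 20% decrease" in stroke, myocardial injury or death, at α = 0.05 and 80% power.
- **Outcome Measures:** the trial's own MACE is a different composite: stroke, coma, myocardial infarction, heart block and cardiac arrest. PND and mortality stand beside it.

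No section gives an expected rate, or a power calculation, for MACE, PND or mortality.

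**The concern.** Two neighbouring paragraphs of the Discussion cannot both stand. One says power is adequate for major complications. The other gives a requirement for a complications composite that is more than two and a half times the planned enrolment (5,400 / 2,036 = 2.65).

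The complication outcomes will be formally tested as secondary outcomes. If adequate power for them is on record, a non-significant MACE or mortality result can be read as showing that withholding or continuing makes no difference. The sample size was not chosen to support that reading.

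**Working it through.** **Inputs from the article.** Hypotension 28.6% v 22.88%; α = 0.05, two-sided (Statistical Analysis: "with a two-sided *P*-value < 0.05 indicating a statistically significant difference"); power 80%; 1:1 allocation; 916 evaluable and 1,018 enrolled per group; more than 5,400 patients in total for a 20% reduction in the composite. The composite's base rate is not given.

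**Step 1: reproduce the plan's own figure.** Pooled two-proportion formula without continuity correction, with p̄ = (p₁ + p₂)/2:

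n = [1.960·√(2p̄(1−p̄)) + 0.842·√(p₁(1−p₁) + p₂(1−p₂))]² / (p₁−p₂)²

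With p₁ = 0.286, p₂ = 0.2288, p̄ = 0.2574: n = (1.2118 + 0.5193)² / 0.0572² = 915.9, so 916 per group. Then 916 / 0.90 = 1,017.8, so 1,018. Both figures reproduce, which identifies the method.

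**Step 2: power for the cited composite without a base rate.** At a fixed effect, the detectable signal scales with the square root of the sample size, so

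power ≈ Φ[(1.960 + 0.842)·√(1,832 / N) − 1.960], where 1,832 = 2 × 916.

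- N = 5,400 evaluable: Φ(2.802 × 0.5825 − 1.960) = Φ(−0.328) = 37.1%.
- N = 5,400 × 0.90 = 4,860 evaluable: Φ(2.802 × 0.6140 − 1.960) = Φ(−0.240) = 40.5%.

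**Step 3: check with the formula of Step 1.** Solve it backwards for the control risk at which a 20% relative reduction needs N patients, then compute power at 916 per group.

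| Reading of 5,400 | Implied control risk | Power, 916 per group | Relative reduction for 80% power |
|---|---|---|---|
| Evaluable total | 11.7% | 37.1% | 33% |
| Includes 10% drop-out | 12.8% | 40.5% | 32% |

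**Step 4: sensitivity.**
- With no drop-out at all (1,018 evaluable per group), the two readings give 40.5% and 44.1%.
- With a continuity-corrected formula used to derive the implied risk, they give 38.1% and 41.6% at 916 per group.
- The article says more than 5,400, so these values lean high. A requirement of 6,000 evaluable would give 34.0%.

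**Step 5: the trial's own outcomes (control risks assumed, not from the article).** Power for a 20% relative reduction at 916 per group:

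| Assumed control risk | Power |
|---|---|
| 10% | 32% |
| 5% | 18% |
| 2% | 9% |

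All of these use an unadjusted comparison at 0.05. The planned covariate adjustment and the Benjamini-Hochberg correction for secondary outcomes are not modelled.

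**The case against.** The strongest reply is that the article discloses the limitation itself. It makes complications secondary, gives the size that powering for them would take, and rests no design element on the disputed words, which form part of one sentence about novelty. Much of this stands, and it limits the severity. It does not rescue the sentence: the limitations paragraph explains why complications are not primary, but it does not withdraw the power claim and in fact supplies the figure that contradicts it.

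A second reply is that the composite behind the 5,400 figure is not the trial's MACE. This is correct and limits what can be claimed. A reader might infer that power is at most 40% for every complication outcome. The documents do not support that. The 37–40% belongs to stroke, myocardial injury or death, and power depends on event rates the article does not give. A commoner outcome would have more power: at a control risk of 28.6% it is 80%, as in the primary calculation. A rarer one would have less.

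A reader might also infer that the article plans to treat a null complication result as evidence of no effect. No section says so; the risk lies in how the power claim could later be used.

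**Conclusion.** The claim of adequate power for major complications is unsupported, and it conflicts with the article's own figure. For a 20% reduction in stroke, myocardial injury or death, power at 916 per group is about 37% to 40%, depending on whether 5,400 excludes or includes 10% drop-out, against the 80% used for the primary outcome. This assumes that 5,400 is a total over both groups and was derived by a standard two-proportion calculation. It hardly depends on the base rate, since the rate-free and rate-based checks agree.

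For MACE, PND and mortality the conclusion is only that power has not been established. The figures for 10%, 5% and 2% illustrate assumed risks.

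Severity is minor to moderate. The sample size for hypotension reproduces exactly, and nothing here calls for more patients or a different primary analysis.

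**What to change.** In the strengths paragraph of the Discussion, restrict the adequate-power statement to perioperative hypotension by deleting *and major complications*.

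In the limitations paragraph, add that the trial is not powered for the complication outcomes. If a figure is given, tie it to its composite and sample size: about 37–40% power at 916 evaluable per group for a 20% relative reduction in stroke, myocardial injury or death. The figure should not be attached to MACE, PND or mortality unless expected rates for them are stated.

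The cost is text only: no extra patients and no change to outcomes, tests or the primary sample size. The one loss is a less favourable description of the trial.
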